#### Secondary Outcomes

The secondary outcomes are patient motivation and intent. We will administer the CKD Self-Efficacy Scale [10], the Patient Activation Measure [11], and the Kidney Failure Treatment Preferences [12] before the intervention, immediately after the intervention, and at 30 days after discharge. We will administer the General Health Knowledge and Intent survey, an investigator-developed instrument, to assess RRT preferences and commitment to CKD self-care activities, including intent to seek a nephrologist, noncatheter dialysis access initiation, and completion of a transplant evaluation. Each patient will be contacted 30 days after discharge to discuss their commitment to each selected health goals, barriers, and treatment plan.

### Data Collection and Management

We will retrieve baseline survey information from the Hospitalist Project, which includes patient demographics and comorbidities. The initial trial data will be collected, stored, and saved in Google Forms with linked Google Sheets for the pretest and posttest surveys on the computer. The RA will photograph and save participants’ written packet responses digitally. The RA will deidentify the packet responses and save them according to their initials, study visit date, and enrollment number. We will ensure participant responses remain confidential. Information about the patient’s medical status, enrollment, and participation will be maintained through a password-encrypted file.

The RA will use password-encrypted laptops to conduct the study. The participant’s responses on the study packet will be photographed, deidentified, and saved in a password-encrypted digital folder. The analysis file will not be attached to protected health information to protect patient privacy. We will conduct analysis in a locked office with a password-protected computer. All transcripts and surveys will be deidentified.

### Statistical Methods

The planned total sample size is 170 (85 per group), which accounts for participant dropout due to unexpected discharges, changes in clinical status, or study disenrollment. The primary outcome will be measured by the change in baseline observed via the pretest, posttest, and follow-up surveys. Using a 2-sample, 2-tailed *t* test, a total of 154 (77 per group) participants is required to obtain >90% power to detect at least a 10% difference with the most conservative SD of 21% with a 1-sided type-1 error of 5%.

Our team will use the paired, 2-tailed *t* test with a Bonferroni adjustment for multiple comparisons with the usual hospital care and computerized adaptive education groups. We will use one-way ANOVA and chi-square tests to examine the significance between the usual hospital care and computerized adaptive education groups. This will determine whether there is a statistically significant difference between the two groups. We will also determine if the difference between observed and expected data is because of chance or a relationship between the usual health care and computerized adaptive education groups.

Data analysis will take place in an UCMC office. We will continue to monitor patient medical records after the study to determine whether they may be later included or excluded from the study.

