**Methods:**

We will screen, recruit, and enroll hospitalized patients who self-identify as African American and have advanced CKD based on their estimated glomerular filtration rate. Eligible patients who verbally consented will be randomly assigned into either the computerized adaptive education intervention group or the control group (usual hospital care). Patients in the intervention group will receive a culturally tailored, adaptive education module. To analyze pretest, posttest, and follow-up survey results on patient CKD knowledge, ESKD treatment options, and health goals, we will use a paired, 2-tailed *t* test with a Bonferroni adjustment for multiple comparisons.

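### The stated power above 90% holds only at a one-sided 5% level; for the two-tailed test named in the same sentence it is about 84% at 77 per group

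*Protocol article*

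**What the plan says.** The sample-size paragraph under Statistical Methods in the protocol article opens its calculation with "Using a 2-sample, 2-tailed *t* test" and concludes that "a total of 154 (77 per group) participants is required to obtain >90% power". The target is "to detect at least a 10% difference", "with the most conservative SD of 21% with a 1-sided type-1 error of 5" per cent. Planned enrolment is 170, or 85 per group, to allow for dropout.

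The next paragraph of that section turns to the analysis. It names a paired, two-tailed t test with a Bonferroni adjustment, and then one-way ANOVA and chi-square tests for comparing the two groups. The abstract's Methods paragraph says of the knowledge, treatment-option and health-goal results that "we will use a paired, 2-tailed *t* test with a Bonferroni adjustment for multiple comparisons". Neither place says how many comparisons the adjustment covers.

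**The concern.** A two-tailed t test and a one-sided 5% error rate cannot both govern one calculation. At a fixed sample size, the choice between them changes the power materially.

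Two things are at stake. First, a reader judges a null result by the stated power. If the test is two-sided, the chance of missing a true 10-point difference is well above the 10% that the article implies. Second, the error level of the primary test is left open. A favourable result with a two-sided p value between 0.05 and 0.10 could be called positive by citing the one-sided level or negative by citing the two-tailed test. That choice should not remain open once the data are seen.

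**Working it through.** **Inputs**, all from Statistical Methods: difference 10 points; SD 21 points; 77 evaluable per group (85 enrolled); alpha 5%; 1:1 allocation. The standardised difference is 10/21 = 0.476.

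**Formulas.** For a two-sample comparison with n per group, the standard error is SD × √(2/n). Approximate power is Φ(difference/SE − z), with z = 1.645 for one-sided 5% and 1.960 for two-sided 5%. Approximate n per group for 90% power is 2 × (z + 1.282)² × (SD/difference)². The exact figures below use the noncentral t distribution.

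**Step 1: reproduce the stated figure.**
- One-sided n: 2 × (1.645 + 1.282)² × 2.1² ≈ 75.5, so 76. The noncentral t gives 76.2, so 77.
- At 77 per group, SE = 21 × √(2/77) = 3.384 and 10/3.384 = 2.955. Power is Φ(2.955 − 1.645) = 90.5%; the noncentral t gives 90.3%.

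The stated 77 per group and power above 90% therefore come from the one-sided 5% level.

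**Step 2: the two-tailed test named in the same sentence.**
- At 77 per group, power is Φ(2.955 − 1.960) = 84.0%; the noncentral t gives 83.5%.
- At 85 per group with no dropout, SE = 3.221 and power is Φ(3.104 − 1.960) = 87.4%; the noncentral t gives 87.0%.
- For 90% power, 2 × (1.960 + 1.282)² × 2.1² ≈ 92.7, so 93. The noncentral t gives 93.6, so 94 per group, or 188 evaluable against 170 planned to enrol.
- The difference detectable with 90% power at 77 per group is about (1.960 + 1.282) × 3.384 = 10.97 points; the noncentral t gives 11.04. That is about 11.0 points rather than 10.

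The risk of missing a 10-point difference is thus 100 − 83.5 = 16.5%, against 100 − 90.3 = 9.7% on the one-sided basis, a ratio of about 1.7.

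**Step 3: the between-group test the article plans.** With two groups, the one-way ANOVA F statistic equals the square of the pooled t statistic. Its 5% test is the two-sided 5% t test, so the Step 2 figures apply to it.

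**Step 4: Bonferroni, conditional.** The number of comparisons k is not given, so k is assumed, as is the application of the adjustment to the primary group comparison. Noncentral t, two-sided alpha 5%/k:

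| Assumed k | Power, 77 per group | Power, 85 per group |
|---|---|---|
| 1 (no adjustment) | 83.5% | 87.0% |
| 2 | 75.5% | 79.9% |
| 3 | 70.3% | 75.3% |

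**Step 5: sensitivity to the SD.** The article calls 21% conservative. Two-sided power at 77 per group is 86.9% for an assumed SD of 20 and 90.1% for an assumed SD of 19.

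**The case against.** The strongest defence has four parts.

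- **The error rate is disclosed.** The one-sided level is printed, so a careful reader can see what the figure rests on, and the primary hypothesis is directional. This does not resolve the conflict. The sentence also names a two-tailed test, and no one-sided analysis is planned anywhere in the article.
- **The shortfall is modest.** Power of 83.5% to 87.0% is not inadequate, and an SD of 19 would restore 90% two-sided. This stands as a limit on the severity. It does not save the stated figure, which is tied to an SD of 21.
- **Bonferroni may not touch the primary comparison.** The text attaches it to the paired test, whereas the calculation concerns a two-sample test and the group comparison is assigned to ANOVA and chi-square without mention of an adjustment. A reader might infer that the primary test is certainly Bonferroni-adjusted and has power of 75% or less. The article does not establish that. The abstract does apply the adjusted paired test to knowledge results, so the opposite cannot be assumed either.
- **Not every named analysis is described as two-tailed.** ANOVA and chi-square carry no such label. For the continuous group comparison the point survives through the equivalence in Step 3.

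A reader might also infer that the trial will be tested one-sided at 5%, doubling the usual error rate in the favourable direction. The article does not say so. That would follow only if the conflict were settled by adopting the one-sided level for the analysis.

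**Conclusion.** The concern holds in a limited form. The claim of more than 90% power is correct at one-sided 5% and wrong for the two-tailed test named alongside it. With the article's own difference and SD, two-sided power is about 84% at 77 per group and 87% if all 85 are evaluable. Nothing else in the article reconciles the two statements.

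This conclusion needs only the article's inputs and a two-sided 5% level on one between-group comparison. The further loss under Bonferroni (to 75.5% or 70.3% at 77 per group) is conditional on the adjustment reaching that comparison and on an assumed two or three comparisons. The result does not show that the trial is inadequate or must enrol more participants. It shows that the stated power is too high for the named test and that the primary error level is unsettled.

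**What to change.** Before any analysis, in the sample-size and analysis paragraphs:

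1. Name a single primary between-group comparison and test it at a two-sided 5% level. Delete the one-sided wording.
2. State that Bonferroni does not apply to that comparison. If it does, give the number of comparisons and restate power at the adjusted level.
3. Restate power as about 84% at 77 per group and 87% at 85 per group, for a 10-point difference and an SD of 21. The difference detectable with 90% power at 77 per group, about 11.0 points, can be added.

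The cost is a change of wording and a less favourable power figure, with no added participants. The Results section reports that data analysis has not occurred, so the change can still be made in advance.

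As an option, the primary comparison could be adjusted for the pretest score. If 21% is the SD of the score itself, the residual SD is 21 × √(1 − r²). For an assumed pretest-posttest correlation r of 0.3, 0.5 or 0.7 this is 20.0, 18.2 or 15.0, and two-sided power at 77 per group is 86.8%, 92.4% or 98.4%. The outcome is defined as a change, so 21% may already be the SD of change, in which case these figures do not apply. The correction above does not depend on this option.

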### Primary Hypothesis

Our primary hypothesis is that the computerized adaptive education will be more effective than usual hospital care in improving knowledge about CKD, CKD self-care, and RRT options (primary outcome).

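### The test tied to the knowledge outcome is a within-arm paired t test, and the plan does not say which between-group test decides the primary hypothesis

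*Protocol article*

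**What the plan says.** The Primary Hypothesis section makes a comparison between arms: "computerized adaptive education will be more effective than usual hospital care in improving knowledge about CKD, CKD self-care, and RRT options (primary outcome").

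Statistical Methods defines the outcome as a change: "The primary outcome will be measured by the change in baseline observed via the pretest, posttest, and follow-up surveys". It sizes the trial with an unpaired test: "Using a 2-sample, 2-tailed *t* test, a total of 154 (77 per group) participants is required".

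For the analysis, the same section first names a paired test: "Our team will use the paired, 2-tailed *t* test with a Bonferroni adjustment for multiple comparisons with the usual hospital care" and the education arm. It then adds: "We will use one-way ANOVA and chi-square tests to examine the significance between the usual hospital care and computerized adaptive education groups". The sentence after that gives the purpose of these added tests, which is to establish whether the two groups differ.

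The Methods paragraph of the Abstract covers the pretest, posttest and follow-up results on knowledge, treatment options and health goals. It names one test only: "we will use a paired, 2-tailed *t* test with a Bonferroni adjustment for multiple comparisons".

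No test is labelled main or primary anywhere in the article.

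**The concern.** A paired t test on pretest and posttest scores asks whether the mean change within one arm is zero. That change contains any effect of the education, but also the effect of answering the same survey twice and of the attention received. Both arms take the survey before and after, and both receive material, so some gain in both arms is plausible. Only a comparison of the arms removes the shared part.

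The article attaches the within-arm test to the knowledge outcome and leaves the between-group test unattached. A reader following the Abstract would carry out an analysis that does not answer the primary hypothesis. A reader of Statistical Methods could choose either route. The risk is that a significant gain in the intervention arm, beside a non-significant one in the control arm, is reported as evidence that the education works better. The research team is not blinded, so it is worth settling the choice before the data are analysed.

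**Working it through.** **1. Which test gives 77 per group?**

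Inputs from Statistical Methods: difference 10, SD 21, power above 90%, 1-sided type 1 error 5%. I read 10% and 21% as points on one absolute scale.

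- Unpaired, one-sided, normal approximation: n = 2 × (1.645 + 1.282)² × 21² / 10² = 75.5, so 76 per group. The exact t calculation gives 76.2, so 77. Power at 77 is 90.3%. The stated figure is reproduced.
- Unpaired, two-sided 5%: 94 per group by the t calculation (power at 77 is 83.5%). Not reproduced.
- Paired, SD of differences 21: 49 pairs two-sided, 40 one-sided. Not reproduced.

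The sample size therefore belongs to an unpaired, one-sided comparison of two groups and not to the paired test.

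**2. Is there a matching between-group test in the plan?**

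Yes, in one-way ANOVA. With two groups, F = t², so its two-sided p value is that of the two-sample t test. In 20,000 simulated trials the two p values differed by no more than about 10⁻¹⁵. What is missing is a statement that this test is applied to the knowledge change, at a given time point, as the deciding analysis.

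**3. What if within-arm results were used to decide?**

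Assumptions: no true difference between arms, 77 per arm, SD of change 21, each paired test two-sided at 5%. The shared gain g is not in the documents, so a range is shown.

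The standard error of an arm's mean change is 21/√77 = 2.393, and the noncentrality is g/2.393. Let p be the probability that one arm's paired test is significant. The arms are independent, so the probability that only the intervention arm is significant is p(1 − p).

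| Shared gain g | p | Intervention arm alone significant, p(1 − p) |
|---|---|---|
| 0 | 0.050 | 4.8% |
| 2 | 0.131 | 11.4% |
| 5 | 0.541 | 24.8% |
| 8 | 0.910 | 8.2% |
| 10 | 0.985 | 1.5% |

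At g = 0, half of the 4.8% are significant falls, so about 2.4% are significant gains. At g = 2 the gains alone are 11.1%. From g = 5 upward the distinction is negligible. The comparator is 2.5%: a two-sided 5% between-group test rejects in favour of the intervention that often at every g. In the simulation the two-sample test rejected in 5.0% of trials, both directions together, at g = 5 and at g = 10.

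The table falls again at large gains because the control arm becomes significant too. The intervention arm's own paired test, read without the control arm, is significant in 98.5% of trials at g = 10.

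**4. What would a pretest covariate add?**

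Assume here that 21 is the SD of the score itself, which the article does not say, and let ρ be the pretest-posttest correlation. The change score has SD 21√(2(1 − ρ)), and ANCOVA has residual SD 21√(1 − ρ²). Power for a 10-point difference, two-sided 5%, 77 per group:

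| ρ | SD, change | Power, change | SD, ANCOVA | Power, ANCOVA |
|---|---|---|---|---|
| 0.3 | 24.8 | 70% | 20.0 | 87% |
| 0.5 | 21.0 | 84% | 18.2 | 92% |
| 0.7 | 16.3 | 97% | 15.0 | 98% |

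**The case against.** A reader might infer that the paired t test is the trial's main analysis and that the plan has no valid between-group test. The text does not support that. Nothing calls the paired test main, and Statistical Methods sends the question of a group difference to ANOVA and chi-square. Since ANOVA with two groups is the two-sample t test, the method behind the 77 per group is present under another name. Nor does the article clearly propose pairing patients across arms: the Abstract ties the paired test to repeated surveys, where it is an ordinary within-patient summary.

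A reader might also take the 25% as the plan's false-positive rate. It is not. The article states no rule that success is declared from the intervention arm alone, and p(1 − p) cannot exceed 25%, so the 5-point gain lies almost exactly at the worst case. The rest of the range is much lower.

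Lastly, one may say that assigning tests to outcomes is work for the analysis plan, that an abstract condenses, and that comparing change scores between randomised arms is valid without a covariate. The last of these stands in full: the absence of ANCOVA is a lost gain in precision, not an error. The first two stand only in part. The point does not rest on missing detail. The article states a test for the knowledge results, and that test does not fit its own hypothesis or its own sample size.

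**Conclusion.** The concern holds in a limited form. The only test tied to the knowledge outcome is a within-arm test, while the hypothesis and the sample size are between-group. The suitable test is named but not assigned, so the plan does not say which result decides the primary hypothesis.

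The consequence is conditional. If within-arm results were used to decide, a trial with no true difference would show significance in the intervention arm alone in between 1.5% and 25% of cases over shared gains of 0 to 10 points. This rests on 77 per arm, a change SD of 21 and gains that are assumed. If the ANOVA on the change score is what is meant, the error rate is as intended and the 77 per group stands at its stated one-sided level.

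This should be fixed, but it does not invalidate the design. Whether the test is one- or two-sided is a separate matter that the article must also reconcile, because the sample size sentence describes the test as 2-tailed with a one-sided error.

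**What to change.** In Statistical Methods, name one between-group comparison of the knowledge score, on one stated instrument and at one stated time point, as the primary analysis. ANCOVA is preferable: a linear model of the score at that time point on randomised arm with the pretest as covariate, reporting the adjusted mean difference with its 95% confidence interval. A two-sample comparison of change scores would also be valid, and the ANOVA sentence can be reworded to say that if the team prefers it.

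Label the paired t tests as descriptive within-arm results, keep chi-square for categorical items, and make the Abstract name the same primary test.

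The cost is wording only. The pretest is already part of the study procedures in both arms, no new data are needed, and the Results section says that no analysis had been done, so on the article's account the choice can still be fixed before results are seen.

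### The abstract names only a paired t test and Statistical Methods lists it first, although the primary hypothesis compares two independent arms; the between-group ANOVA also listed is given no outcome variable, time point or priority

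*Protocol article*

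**What the plan says.** The Primary Hypothesis section sets up a contrast between arms: "the computerized adaptive education will be more effective than usual hospital care in improving knowledge about CKD".

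The sample size in Statistical Methods follows from that contrast: "Using a 2-sample, 2-tailed *t* test, a total of 154 (77 per group) participants is required", for ">90% power to detect at least a 10% difference with the most conservative SD of 21" per cent, at a 1-sided type I error of 5%. The section describes the primary outcome as change from baseline across the pretest, posttest and follow-up surveys.

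The analysis paragraph of the same section begins with a different test: "Our team will use the paired, 2-tailed *t* test with a Bonferroni adjustment for multiple comparisons", applied to comparisons with the two study groups. It continues: "We will use one-way ANOVA and chi-square tests to examine the significance between the usual hospital care and computerized adaptive education groups". The purpose it gives is: "This will determine whether there is a statistically significant difference between the two groups". The two-sample t test of the sample-size sentence is not named again.

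The Methods part of the abstract gives one analysis for the pretest, posttest and follow-up results: "we will use a paired, 2-tailed *t* test with a Bonferroni adjustment for multiple comparisons". It names no between-group test.

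**The concern.** A paired t test compares two measurements on the same person, or on matched people. Neither reading of it here answers the primary hypothesis.

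- **Within an arm, pretest against posttest.** This tests whether that arm changed. It says nothing about whether one arm changed more than the other.
- **Between arms.** No pairs exist. The Randomization section allocates individuals by odd or even random number without matching, and the Results section reports 50 control and 46 intervention patients with both surveys.

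The within-arm reading matters because both arms repeat the knowledge survey after their education material (Intervention Group and Control Group sections), so some gain on retest is plausible in both. A within-arm test credits that gain to whatever the arm received. Significance in one arm and not in the other is then weak evidence of a difference, and significance in both arms leaves the hypothesis open. A Bonferroni adjustment lowers the threshold of each paired test but does not turn it into a comparison of arms.

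**Working it through.** **1. The plan's own figure.** Inputs from Statistical Methods: difference 10, SD 21 (both read as percentage points), power above 90%, 1-sided 5%.

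Normal approximation, two samples: n per arm = 2 × (z₀.₉₅ + z₀.₉₀)² × SD² / difference² = 2 × (1.645 + 1.282)² × 441 / 100 = 75.5, rounded up to 76. The exact noncentral t calculation gives 77 per arm with 90.3% power. The stated 77 is reproduced.

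A paired test with the same 10 and 21 would need 40 (1-sided) or 49 (2-sided) patients in a single arm. Of the calculations tried, only the two-sample, 1-sided one gives 77, so the design rests on a between-arm test.

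**2. What happens if conclusions come from the paired tests.** Assumptions: 77 per arm, SD of change 21 (the document does not say that its SD is the SD of change), 2-sided 5% in each arm, and the same mean gain in both arms, so the true arm difference is zero.

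Standard error of the mean change = 21 / √77 = 2.39. Let p be the chance that one arm shows a significant improvement (noncentral t, 76 degrees of freedom). The arms are independent, so the chance of intervention improved, control not, is p(1 − p).

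| Common gain (points) | p per arm | Intervention only, p(1 − p) |
|---|---|---|
| 0 | 0.025 | 2.4% |
| 2 | 0.128 | 11% |
| 3 | 0.235 | 18% |
| 4.7 | 0.492 | 25% |
| 6 | 0.697 | 21% |
| 8 | 0.910 | 8% |
| 10 | 0.985 | 1.5% |

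The product p(1 − p) cannot exceed 0.5 × 0.5 = 25%, reached where p = 0.5, at a gain of about 4.75 points. A simulation of 50,000 trials at a gain of 4.7 gave 25.1% for this pattern. In the same simulated trials the two-sample test rejected in 5.2%, close to its nominal 5%.

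**3. Effect of Bonferroni.** With two tests at 0.025 each, the rates are 7.2% at a gain of 2, 24.5% at 5, 24.2% at 6, 12.6% at 8 and 3.0% at 10. The peak moves to a larger gain and stays at about 25%, because the bound on p(1 − p) does not depend on alpha.

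**4. The opposite error.** Take gains of 18 and 8 points, a true difference of 10. The paired test is significant with probability above 0.999 in the intervention arm and 0.910 in control. Both are significant about 91% of the time, and the paired tests alone would not show the difference.

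**5. The listed ANOVA.** For two groups and the same variable, one-way ANOVA and the equal-variance two-sample t test give the same p value (0.189 from both in a simulated data set). If run on change scores, the ANOVA is the sizing test under another name. The text does not say whether it is run on change or on posttest score, or at which survey.

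**The case against.** The strongest reply is that the plan already contains the right test. Directly after the paired-test sentence, Statistical Methods lists a one-way ANOVA between the groups and says of the between-group tests: "This will determine whether there is a statistically significant difference between the two groups". On change scores that ANOVA matches the sample-size test. Chi-square would naturally serve categorical items and need not compete for the knowledge score. The abstract is a condensed summary, and the labelling of one primary test is often left to an analysis plan, which is not shown here.

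Much of this stands. A reader might infer that the between-group hypothesis is assigned only to a within-arm test, or that improvement in one arm alone will be reported as an education effect. The document supports neither reading: a between-group test is planned, and no sentence states a one-arm-only decision rule. The 25% is also a worst case, and it applies only if the ANOVA is set aside. Nor is it certain that all retests fall in one session, since the Intervention Group section only encourages completion in one visit.

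What remains is in the text itself and is not detail left out. The article names its tests, puts first one that cannot answer its hypothesis, applies it to comparisons with the two groups, and names it alone in the abstract. The ANOVA is tied to no variable or time point and is given no precedence.

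**Conclusion.** The point holds as an ambiguity with a wrong test placed in front. The hypothesis and the sample size are between-arm, the test named first (and alone in the abstract) is paired, and the valid between-arm test is listed without variable, time point or priority.

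Reporting a gain in one arm only as an effect is therefore a risk, not the planned rule. If it happened with no true arm difference, the misleading pattern would occur in about 1.5% to 25% of trials for common gains of 2 to 10 points, against a nominal 5% for the two-sample test. This rests on 77 per arm, independent arms with equal mean gains, and 21% taken as the SD of change in percentage points. The document gives no figure for the retest gain, so the position within the range is unknown.

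**What to change.** In Statistical Methods and in the abstract, state that the primary hypothesis is decided by one between-arm comparison of change in knowledge score at one named time point. It can be a two-sample t test (equivalent to the listed one-way ANOVA on change) or an ANCOVA adjusted for the pretest score. Report the arm difference with a confidence interval that matches the stated alpha. Make the paired within-arm tests descriptive, with no efficacy conclusion drawn from them, and limit chi-square to categorical outcomes.

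The interval needs care because the section calls the sizing test 2-tailed but uses a 1-sided 5% error. At 1-sided 5%, 77 per arm gives the 90.3% power shown above. At 2-sided 5%, with a 95% interval, 77 per arm gives 83.5%, and 90% would need 94 per arm, more than the 85 planned. The choice should be stated.

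The cost is a few sentences and no change to data collection. The sample size is unaffected if the stated 1-sided alpha is kept. Both the abstract and the Results section say that no analysis has occurred, so the change can be made without knowledge of the results. The downside is that within-arm p values can no longer be offered as evidence of effect.

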### Outcomes

#### Primary Outcome

The primary outcome of this study is the changes in patient knowledge, attitudes, and behavior about CKD and RRT. To evaluate CKD and CKD self-care knowledge, we will use a modified Kidney Knowledge Survey; the CKD Self-Management Knowledge Toolkit, which is a validated instrument [8,9]; and an investigator-developed ESKD knowledge survey. We will measure the change from the baseline observed via the pretest, posttest, and follow-up surveys. The pretest and posttest surveys comprise 20 mixed format multiple-choice and Likert-scale questions (ranging from strongly agree to strongly disagree; from no knowledge to a great deal of knowledge; and from extremely unlikely to extremely likely) to examine the patient’s basic understanding of their health, general CKD knowledge, and health management.

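### The plan adjusts for multiple comparisons with Bonferroni, although Holm's step-down version holds the same family-wise error and never rejects less; the gain is modest and depends on a family size the article does not state

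*Protocol article*

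**What the plan says.** The Statistical Methods section of the protocol article plans a paired, two-tailed t test "with a Bonferroni adjustment for multiple comparisons"; the Abstract says the same. Neither place says how many comparisons make up the family or which they are. The between-group tests, one-way ANOVA and chi-square, appear in the next sentence with no adjustment stated.

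More than one comparison is plausible from the Primary Outcome section. It names three knowledge sources (a modified kidney knowledge survey, a self-management knowledge toolkit and an investigator-developed ESKD survey) and adds: "We will measure the change from the baseline observed via the pretest, posttest, and follow-up surveys".

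The sample size rests on a single comparison. It asks for 77 per arm, 154 in all, to reach more than 90% power. The target effect is worded "to detect at least a 10% difference"; the assumed variability is "the most conservative SD of 21"%; and the error rate is one-sided: "with a 1-sided type-1 error of 5"%. The recruitment target adds a margin: "The planned total sample size is 170 (85 per group), which accounts for participant dropout". The Results section states that no data analysis has taken place.

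**The concern.** An unqualified Bonferroni adjustment ordinarily means that each of m tests is judged at 0.05/m, whatever the other tests show. Holm begins at that same threshold and relaxes it after each rejection, at no cost in family-wise error. The Primary Hypothesis predicts improvement in knowledge of CKD, of self-care and of treatment options together. That is the pattern in which Bonferroni's fixed threshold misses real effects that Holm would declare. What is at stake is power for the second and later findings in a family. The validity of the error control is not at stake.

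**Working it through.** **Inputs from the article:** difference 10 points, SD 21, 77 per arm, all from Statistical Methods.

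**Assumptions, not in the article:** family size m = 2, 3 or 6 (for example 3 instruments × 2 changes = 6); correlation 0.5 between tests; two-sided family-wise 5%; SD of within-arm change 21; a smaller change of 6 points for one scenario.

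**1. The plan's own figure.** The between-arm noncentrality is (10/21) × √(77/2) = 2.955. At one-sided 5%, power = Φ(2.955 − 1.645) = 0.905 by the normal approximation and 0.903 by the noncentral t. The t-based requirement is 76.2, so 77 per arm. The stated figure reproduces. It is for one unadjusted one-sided test; two-sided, power at 77 per arm is about 0.84.

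**2. The two procedures.** Bonferroni rejects when p ≤ 0.05/m. Holm orders the p values and rejects the j-th smallest if it and all smaller ones satisfy p(j) ≤ 0.05/(m − j + 1). For j = 1 this is 0.05/m, the Bonferroni threshold. So both give at least one rejection in exactly the same data sets (m = 2, between-arm: about 89% for both). From j = 2 on, Holm's threshold is larger, so it rejects everything Bonferroni rejects and sometimes more.

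**3. Paired tests, where the text places the adjustment.** Noncentrality for a 10-point change is (10/21) × √77 = 4.179. Bonferroni power is Φ(4.179 − z), with z the two-sided critical value at 0.05/m. Holm power is from simulation (400,000 replicates), all m changes being real.

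| m | z | Bonferroni | Holm | Gain (points) |
|---|---|---|---|---|
| 2 | 2.241 | 97.4% | 98.5% | about 1 |
| 3 | 2.394 | 96.3% | 98.3% | about 2 |
| 6 | 2.638 | 93.8% | 97.7% | about 4 |

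In a mixed family with m = 6, three changes of 10 points and three of 6, the 6-point noncentrality is (6/21) × √77 = 2.507. Bonferroni power for each 6-point change is Φ(2.507 − 2.638) = 45%, against 62% with Holm, a gain of about 17 points. The 10-point changes in that family gain just under 2 points, from about 94%.

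**4. Between-arm tests, if the adjustment is applied there too.** Noncentrality is 2.955 and all m effects are real.

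| m | Bonferroni per test | Holm per test | Gain (points) |
|---|---|---|---|
| 2 | 76% | 81% | about 5 |
| 3 | 71% | 79% | about 7 |
| 6 | 62% | 73% | about 10 |

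**5. Sensitivity.** At m = 3 between arms the gain is 9 points at correlation 0 and 6 points at 0.8. If only one of three effects is real, the gain almost vanishes (71.1% against 71.2% at correlation 0.5).

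**6. Error control.** Under the global null with m = 6 and correlation 0.5, family-wise error is 4.1% for both. With two real between-arm effects and one null it is 1.7% for Bonferroni and 3.7% for Holm. Both stay under 5%.

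**The case against.** The strongest reply is that Bonferroni is valid, prespecified and conservative, and that no figure in the article becomes wrong because of it. That stands: this is a better available choice, not an error or a contradiction.

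Three further points also stand. The article does not state m, so the loss cannot be derived from it. The correlation, the SD of change and the 6-point change are assumptions. The text attaches the adjustment to the paired tests, where power at a 10-point change is already 94% or more, so the larger between-arm gains describe an adjustment the text does not specify. In addition, the article does not call its Bonferroni single-step; that is the ordinary meaning of the unqualified name, and a fuller document could define it differently.

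A reader might infer that Bonferroni is always the weaker method and gives power away for nothing. The documents do not support that. The chance of at least one rejection is identical, the gain is negligible when only one effect is real, and single-step Bonferroni offers simple matching simultaneous confidence intervals and one fixed threshold. The widest gap in simulation is for declaring all comparisons significant at once (between-arm, m = 6: 25% against 51%), but the article never states that as an objective.

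None of this favours Bonferroni for the tests themselves. The article plans significance tests and does not mention simultaneous intervals.

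**Conclusion.** The point holds as an inexpensive improvement. For the tests, Holm dominates Bonferroni: same p values, same family-wise error, no added assumption, never fewer rejections. On the paired tests at a 10-point change the gain is about 1 to 4 points of per-test power for m = 2 to 6, and up to about 17 points for an assumed 6-point change at m = 6. If between-arm comparisons are adjusted as well, it is about 5 to 10 points at the plan's difference and SD. These figures assume correlation 0.5, two-sided 5%, 77 per arm and an SD of change of 21.

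It would be wrong to conclude that the switch repairs the plan's power or its main comparison. Two separate problems in Statistical Methods remain: the sample size is computed at an unadjusted one-sided 5% while the tests are two-tailed and adjusted, and the adjustment is attached to paired tests although the Primary Hypothesis is between groups.

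**What to change.** In the Abstract and in Statistical Methods, name the Holm step-down Bonferroni adjustment in place of the Bonferroni adjustment, and do so before any data are analysed. List the comparisons in each family, since Holm is as undefined as Bonferroni without that list. Report Holm-adjusted p values together with 95% confidence intervals labelled as unadjusted.

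The cost is a few words and no new data. The downside is that Holm has no simple matching simultaneous intervals, so an unadjusted interval may exclude zero while the adjusted p value is above 0.05; the label should make that clear. If the sponsor wants simultaneous intervals, it can keep Bonferroni and give that as the reason.
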